### Setting, participants and eligibility criteria

This study is open to randomized controlled multi-arm trials (Phase II-IV) comparing the effects of pharmacological treatments with antipsychotics to placebo (primary outcome) or any comparator (sensitivity analysis). Individual trial size is not an eligibility criterion. Eligible trials will include adult participants diagnosed with schizophrenia, schizoaffective or schizophreniform disorders. Trials must include PANSS and/or BPRS individual participant data at baseline and outcome. Studies meeting the criteria described in
Table 1 have been requested from
vivli.org (Vivli) and
yoda.yale.edu (YODA Project). Requested studies from the YODA Project are solely sponsored by Johnson & Johnson. In addition, Vivli provides data from the following sponsors: Abbott, AbbVie, Janssen, Johnson & Johnson, Lilly, Otsuka. Previous data checks suggests that we should expect to obtain a pooled sample of ~31 000 participants from 77 studies provided on the Vivli platform (
Table 2).

**Table 1. T1:** Inclusion/exclusion criteria for selecting trials and participant data.

Variable	Inclusion criteria
Study Type	Randomized controlled multi-arm trial
Data Type	Individual Participant Data
Phase	II, IIa, IIb, III, IIIa, IIIb, and IV
Population/Diagnostic Criteria	Participants with Schizophrenia Spectrum Disorders, aged 18 years and older
Treatment	Antipsychotic medication
Comparator	*Placebo* (to establish efficacy) *Active Comparator* (to establish baseline psychometric model)
Active Comparator	*Primary* (standard) *:* first-generation vs second-generation antipsychotics (optionally adding D2 partial agonists as a third category where feasible). *Exploratory:* receptor-based taxonomy as proposed by McCutcheon et al. ^ 21 ^
Outcome	Positive and Negative Syndrome Scale (PANSS) and/or Brief Psychiatric Rating Scale (BPRS)
Covariates	Sex (if available: Age)
Moderator Variable	Sex Stage of illness (sensitivity analysis)
Timing of Outcome Assessment	6 weeks, as per Younis et al. ^ 22 ^/ *4 weeks for sensitivity analysis*

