^ To select the optimal model of schizophrenia, the selection process will be guided by established absolute and relative fit indices, information criteria, and internal consistency metrics, including: the Root Mean Square Error of Approximation (RMSEA; < 0.08), Standardised Root Mean Square Residual (SRMR; < 0.08), Comparative Fit Index (CFI; > 0.95), Tucker-Lewis Index (TLI; > 0.95), Akaike Information Criterion (AIC), Bayesian Information Criterion (BIC), and McDonald’s Omega (acceptable >0.70), following established practices.
^
31,
32
^ Similar to the exploratory approach, confirmatory modelling will be performed for baseline and for the primary post-baseline outcomes. For outcome (post-baseline) measurement models, we will estimate the best-fitting model in the pooled sample and then test invariance across key arm categories (placebo vs active; and where feasible across active-arm classes as defined by the standard classification, with McCutcheon’s taxonomy explored in sensitivity analyses). We will retain the best-fitting baseline and post-baseline model(s) to derive factor scores for downstream treatment-effect estimation in Stage 2.
^
33
^

Measurement invariance, i.e. metric invariance (factor loadings are equal) and scalar invariance (intercepts are equal) across sex will be assessed, and differential item functioning examined by mean, standard error, standard deviation, factor loading scores and
*r
^2^
* values. When invariance is violated, psychometrically optimized models will be examined separated by sub-group (e.g., women and men).

The outcomes of these analyses will then be used for further evaluation and discussion (descriptively) on their differences or similarities in all models and datasets. This procedure will include model structure or item functioning (i.e. dropped items, item loadings on factor). Revised sum scores based on the retained items and weighted scores will then be computed from the best performing baseline and combined outcome model for each measure. These will be used for the stage 2 analysis described in the following sections.

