### Item response theory approaches

Similar to the procedure described above, we will also use IRT approaches.
^
34,
35
^ In IRT, each item is treated as providing information about a latent trait, and items are evaluated by how strongly they discriminate between individuals at different levels of that trait (i.e., higher latent severity increases the probability of endorsing higher response categories). Within an exploratory dataset, we will use non-parametric IRT (Mokken scaling) to assess scalability, dimensionality, and item ordering, and to identify poorly discriminating items. Following recommendations by Meijer and Baneke,
^
36
^ we will evaluate solutions across increasing lower-bound scalability thresholds (c), beginning at c = 0.01 and then stepping by 0.05 (i.e., 0.05, 0.10, 0.15 … up to 0.60), selecting the most interpretable solution. Second, using the confirmatory dataset, we will fit parametric IRT graded response models to estimate item parameters (e.g. discrimination and category thresholds) to identify the best fitting model. Hence, we will compute revised sum scores based on the retained items and generate latent trait (weighted) scores for use in downstream analyses within stage 2.
^
37
^ A detailed description of the analysis principles for the IRT approach is outlined in Byrne’s publications.
^
11,
13
^

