### Exploratory subgroup and sensitivity analyses

Where feasible and supported by data availability, we will explore whether psychometric models and treatment effects vary by sex. Measurement invariance across sex will be assessed within the optimal psychometric models using established procedures. Where invariance is violated, group-specific psychometric models will be estimated, and primary and secondary analyses repeated using sex-specific scores.

To further examine the robustness of findings to potentially important sources of between-trial and clinical heterogeneity, we will attempt to conduct additional exploratory sensitivity analyses:
•Endpoint timing (week 4 vs week 6): Given that acute antipsychotic trials commonly report outcomes around week 6, but earlier endpoints (e.g., week 4) may yield different conclusions.
^
22
^ Therefore, we will, where endpoint timing can be harmonised and sample size allows, repeat analyses stratifying trials by the closest available acute endpoint (week 4 vs week 6).•Stage of illness: Where sufficiently detailed and harmonisable information is available, we will explore whether the best-fitting psychometric model(s), invariance results, and estimated treatment effects differ according to patients’ schizophrenia history (e.g., first-episode/early-phase versus multi-episode/chronic presentations, prior treatment exposure, or other trial-reported indicators of illness course).

These exploratory analyses are motivated by the clinical and methodological need to understand whether modelling choices or trial-design and population differences (such as endpoint timing or illness course) could materially influence inferences about treatment effects. All subgroup and sensitivity analyses will be clearly labelled exploratory, and interpretation will prioritise effect estimates and uncertainty, with transparent reporting of any constraints arising from limited sample sizes, inconsistent variable availability, or restricted harmonisability across trials, consistent with STROBE reporting principles.

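### The statistics named for examining differential item functioning by sex do not compare women and men at equal severity, so the exploratory item-level report cannot separate item bias from a severity difference

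*Protocol article*

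**What the plan says.** In the protocol article, Stage 1, Exploratory and Factor analytic approaches, one sentence contains two things. The first is formal testing: "metric invariance (factor loadings are equal) and scalar invariance (intercepts are equal) across sex will be assessed". The second is an item-level examination: "differential item functioning examined by mean, standard error, standard deviation, factor loading scores", with r² values completing the list. No comparison matched on severity and no size threshold is named for DIF.

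The stated consequence hangs on the first part. The same section has models examined by subgroup when invariance is violated. The section Exploratory subgroup and sensitivity analyses repeats this: "Measurement invariance across sex will be assessed within the optimal psychometric models using established procedures", and then "Where invariance is violated, group-specific psychometric models will be estimated, and primary and secondary analyses repeated using sex-specific scores". The Stage 1 results are to be "used for further evaluation and discussion (descriptively) on their differences or similarities in all models and datasets", and this discussion is said to cover item functioning.

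The section Item response theory approaches adds that "we will fit parametric IRT graded response models to estimate item parameters". That sentence does not mention sex or DIF. It matters here only because it shows that a suitable model is already planned.

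**The concern.** An item functions differently by sex if a woman and a man with the same underlying severity have different expected scores on it. A statistic that is not conditioned on severity cannot show this. If women and men in these trials differ somewhat in severity, item means will differ throughout the scale even when every item works identically in both sexes. In the other direction, an item bias and a severity difference of opposite sign can cancel and leave the means equal.

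At stake is the item-level account of sex differences in the PANSS and BPRS. Items could be described as functioning differently when they reflect only severity, or a shifted item could pass unnoticed.

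**Working it through.** The protocol gives no figure on this point, so there is none to reproduce. The check has two parts.

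**1. Each listed statistic under full invariance.** Take a one-factor model in which item score = intercept + λ × severity + residual. Let intercept, λ and residual variance θ be equal in both sexes, so there is no DIF. Let latent means differ by d and let the latent variance ψ be free to differ.

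- Mean: differs by λ × d. It is non-zero whenever d is non-zero.
- SD: √(λ²ψ + θ). It differs if ψ differs.
- SE of the mean: SD/√n. It differs whenever the numbers of women and men differ.
- r²: λ²ψ/(λ²ψ + θ). It differs if ψ differs, even with equal λ and θ.
- Loading: if unstandardised, it is relevant to DIF that changes the slope, but it is unaffected by a uniform intercept or threshold shift.

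So four of the five can differ with no DIF, and the fifth misses uniform DIF. An example of masking: with λ = 0.6, d = 0.2 and a true intercept shift of −0.12, the mean difference is 0.6 × 0.2 − 0.12 = 0.

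**2. Illustration of size for the item means.**

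Input from the protocol (Setting, participants and eligibility criteria): "pooled sample of ~31 000 participants from 77 studies". Half of that is 15,500. The plan splits the data into exploratory and confirmatory sets, and equal halves are my assumption. Also assumed, and not in the documents: 35% women, d = 0.1 to 0.2 SD, loadings 0.4 to 0.7, no DIF, two-sided 5% level, item SD 1.

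Formula: z = λd / √(1/n_women + 1/n_men); probability of a significant difference ≈ Φ(z − 1.96).

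- N = 15,500: 5,425 women and 10,075 men; standard error √(1/5,425 + 1/10,075) = 0.0168.
  - Low end: 0.4 × 0.1 = 0.04; z = 2.4; probability 66%.
  - High end: 0.7 × 0.2 = 0.14; z = 8.3; probability about 100%.
- N = 31,000: standard error 0.0119; z = 3.4 to 11.8; probability 92% to 100%.

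A simulation gives the contrast with a conditional comparison. It used 30 continuous items, loadings 0.4 to 0.8, 35% women, no DIF and 20 replicates. The conditional test used the true simulated severity, which real data do not supply.

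| N | d | Items differing, unconditional mean | Items differing, conditional on severity |
|---|---|---|---|
| 5,000 | 0 | 2.5% | 3.2% |
| 5,000 | 0.1 | 49% | 3.0% |
| 5,000 | 0.2 | 96% | 4.7% |
| 15,500 | 0 | 3.3% | 6.0% |
| 15,500 | 0.1 | 94% | 5.5% |
| 15,500 | 0.2 | 100% | 6.5% |

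The conditional comparison stays near the nominal 5% throughout. The unconditional one does so only when the sexes do not differ in severity.

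**The case against.** The strongest reply is that the right method is already in the same sentence. Scalar invariance holds intercepts equal while latent means may differ, which is the conditioning on severity that DIF requires. Following up a failed test item by item is ordinary practice, and a condensed article may leave that step to a fuller document. This stands in large part, and it limits the point. It does not remove it, because the article is not silent on DIF: it names the statistics, and no intercept, threshold or severity-matched comparison is among them.

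A second reply is that the mean and SE might be model estimates and not observed item statistics. The text does not say. If intercepts were meant, the wording still needs correcting.

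Third, a reader might infer that the plan would declare items biased whenever their means differ, and would move to sex-specific models on that basis. The documents do not support this. No test of item means and no cut-off is planned, and both places that mention sex-specific models make them depend on violated invariance. Nor is item functioning by sex what the third objective names: that objective asks whether changes found under the new scoring differ by symptom domain and by sex.

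Finally, the probabilities above describe a test that the plan does not propose, under inputs that it does not give. That is correct, and they serve only to show the mechanism.

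**Conclusion.** The point holds as a fault in the stated DIF method. The listed statistics cannot establish or exclude DIF by sex: four can differ without it, and loadings miss a uniform shift. The algebra needs no assumption beyond a factor model.

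The practical size depends on an unknown, the latent severity difference between women and men. In the illustration, differences of 0.1 to 0.2 SD give a 66-100% chance at N = 15,500 that an unbiased item's means differ at the 5% level. At zero difference in latent mean there is no excess.

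The reach is narrow. The sex analyses are labelled exploratory, the discussion of these results is descriptive, and no Stage 2 score, model or decision is stated to depend on the listed statistics. This is an improvement worth making, not a threat to the main comparison of effect sizes.

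**What to change.** Separate the two tasks in the Stage 1 text.

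- Define DIF by sex from the multi-group factor model or the graded response model. Start from the invariant model with latent mean and variance free to differ by sex. Then free one item's loading (or discrimination) and intercept (or thresholds) across sex at a time.
- For each item, report the expected item-score difference at equal severity, and call it DIF only above a size fixed in advance. With samples this large, significance alone would pick out trivial differences.
- Keep means, SEs, SDs and r² by sex in the tables, labelled as description.
- Leave the trigger for sex-specific models as it is, on violated invariance.

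The cost is a few extra runs of models already planned, the choice of one threshold, and a change of wording.

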### Stage 1: Establishing optimal psychometric models of PANSS and BPRS

### Exploratory and Factor analytic approaches

Data will be randomly split into exploratory and confirmatory datasets, as recommended by Lubke and Luningham,
^
27
^ with stratification by treatment group and trial to ensure balanced representation. For stratification and subsequent subgroup/invariance checks, active antipsychotic arms will be coded using literature-standard classification (primary approach: first-generation vs second-generation antipsychotics; where feasible, a third category for D2 partial agonists may be considered). In exploratory analyses, we will additionally code active agents using McCutcheon and colleagues’ data-driven receptor-based taxonomy,
^
21
^ namely muscarinic (M2-M5) receptor antagonists; dopamine (D2) partial agonists and adrenergic antagonists; serotonergic and dopaminergic antagonists; and dopaminergic antagonists. We will ascertain factor models of schizophrenia for baseline (pre-treatment), combined outcome (post-treatment; 6 weeks) and separately for placebo and treatment groups. We will further evaluate measurement invariance across major arm categories (e.g., placebo vs active treatment and, where supported, across active treatment-arm classes) within the best-fitting baseline model(s).

Parallel analysis will be applied to the exploratory datasets to determine symptom dimensionality.
^
28
^ Next, the EFA will be performed, using oblique rotation to allow for correlated symptom domains, to examine the factor structure of the exploratory dataset. Models will be refined iteratively by evaluating factor loadings below 0.3 and/or communalities below 0.4, with poorly performing items removed where justified to achieve stable and interpretable solutions.
^
29
^

In the confirmatory dataset, CFA will be used to formally test candidate psychometric models identified during the exploratory phase. In addition to simple structures derived from EFA, established alternative models, including higher-order and bifactor representations, will be evaluated.
^
30

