### Trial-level analyses

In addition to pooled IPD analyses, treatment effects will be estimated separately within each trial using both conventional and psychometrically-informed outcome scores. For each trial, change from baseline to outcome will be modelled adjusting for baseline severity, and trial-specific SMDs will be calculated for both scoring approaches. The difference between the psychometrically informed SMD and the conventional SMD will be computed for each trial and treated as the trial-level effect of interest. Potential moderators (e.g. sex) may be explored descriptively or within mixed models where data permits.

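### Factor scores are derived from separately chosen baseline and week-6 models with no invariance test over time, so change and response results can mix two scales, although the pooled baseline-adjusted models are not biased

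*Protocol article*

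**What the plan says.** Under Exploratory and Factor analytic approaches the protocol sets out the models to be found: "We will ascertain factor models of schizophrenia for baseline (pre-treatment), combined outcome (post-treatment; 6 weeks) and separately for placebo and treatment groups". The confirmatory step has the same split: "confirmatory modelling will be performed for baseline and for the primary post-baseline outcomes". Both results go forward: "We will retain the best-fitting baseline and post-baseline model(s) to derive factor scores for downstream treatment-effect estimation in Stage 2". The scoring sentence reads: "Revised sum scores based on the retained items and weighted scores will then be computed from the best performing baseline and combined outcome model". Baseline and outcome models are compared with each other only descriptively, including which items were dropped and how items load.

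The factor invariance tests in that section are as follows.
- Baseline model: "We will further evaluate measurement invariance across major arm categories".
- Outcome model: "we will estimate the best-fitting model in the pooled sample and then test invariance across key arm categories".
- Metric and scalar invariance: by sex ("intercepts are equal) across sex will be assessed").

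The Item response theory section says its procedure is similar and names no invariance test. The Network analytic section makes configural invariance across baseline and outcome (or treatment arms) a key goal, with a fallback if it cannot be reached.

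In Stage 2, the pooled models regress the outcome score on treatment with the corresponding baseline abbreviated score as covariate. Under Trial-level analyses, "change from baseline to outcome will be modelled adjusting for baseline severity". Under Secondary analyses: Response, response is defined by cited definitions and compared between conventional and psychometric scoring. Those analyses are labelled exploratory.

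**The concern.** A difference between two visits measures symptom change only if both visits are scored on the same scale. The conventional total meets this automatically. A psychometric score does so only if the item set and weights are common to both visits. The factor section lets items be dropped separately at each visit, keeps both resulting models for scoring, and plans no test of whether the baseline and week-6 models agree. The network section shows that the authors see the need for stability over time, yet the factor and IRT sections do not ask for it.

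The project asks whether psychometric scoring alters estimated effects. The Discussion expects differences of about 10–15%. A shift produced by unequal scoring keys could be mistaken for a benefit or a loss from psychometric refinement.

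**Working it through.** The plan states no figure on this point, so there is none to reproduce. The check asks which Stage 2 quantities depend on a common scale.

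**1. Baseline-adjusted models (algebra).** Let B be the baseline score, O the outcome score and T the arm. The change model is O − B = a + bT + cB + e. Moving B to the right gives O = a + bT + (c + 1)B + e. The treatment coefficient b and the residual e are those of the endpoint model, whatever items make up B. The condition is that the covariate is the same baseline score that was subtracted.

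**2. Single patient (arithmetic; item counts assumed).** Rated 3 on every item at both visits:
- 24 items at baseline: 24 × 3 = 72. 20 items at week 6: 20 × 3 = 60.
- Apparent fall: (72 − 60)/72 = 16.7%.
- Counts reversed: (72 − 60)/60 = 20% apparent worsening.

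**3. Simulated illustration (all inputs assumed).** One data set with 30 items scored 1–7, one factor and 1000 participants per arm. One visit is scored on 24 items and the other on 20 of those 24. Response is a fall of at least 20%, with the baseline score's minimum subtracted in the denominator. SMDs are shown as absolute values.

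| Scoring (baseline/week 6) | d, residual SD | SMD, SD of change | Mean change, control / active | Response, control / active |
|---|---|---|---|---|
| 24/24, same key | 0.510 | 0.440 | −8.9 / −17.9 | 43.4% / 64.9% |
| 24/20 | 0.517 | 0.412 | −19.2 / −27.5 | 68.1% / 82.5% |
| 20/24 | 0.511 | 0.468 | +2.5 / −6.3 | 22.0% / 41.0% |

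- *Residual-SD d:* almost unchanged. With 24/20 the coefficient is −7.354 in both the endpoint and the change model, as step 1 requires.
- *SMD on the SD of change:* 0.412/0.440 = 0.936 and 0.468/0.440 = 1.064, about 6% down or up.
- *Response rates:* they move by more than 17 points in each arm. The difference between arms goes from 64.9 − 43.4 = 21.5 points to 82.5 − 68.1 = 14.4, or 41.0 − 22.0 = 19.0.
- *Odds ratio:* it moves less. (0.649/0.351)/(0.434/0.566) = 2.41 with one key; (0.825/0.175)/(0.681/0.319) = 2.21 with 24/20; (0.410/0.590)/(0.220/0.780) = 2.46 with 20/24.
- *Each score's own minimum subtracted:* this reduces the 24/20 distortion but does not remove it (60.2% and 76.2%).

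**4. Precision in the pooled models (assumed structure).** With five factors, loadings 0.6, factor stability 0.55 and 16 shared items on average, the baseline–outcome correlation falls from 0.521 to 0.505. The residual SD ratio is √(1 − 0.505²)/√(1 − 0.521²) = 1.011, a loss of about 1%.

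**The case against.** The strongest reply is that the plan's main estimates do not need equal scales. That stands. The primary pooled models use baseline only as a covariate, and the trial-level analysis also adjusts for baseline, so step 1 applies. A reader might infer that the trial-level treatment effects, or the second aim as a whole, become uninterpretable. The documents do not support this. The trial-level SMD is affected only if it is standardised by the SD of change, and the article does not name its standardiser.

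Second, Models 2 and 3 call for the corresponding abbreviated score at baseline, with one score listed per method. This leans towards a matched score and stands as evidence of intent. It does not settle the matter, because the factor section retains a baseline and a post-baseline model for scoring. If instead each model were a key applied at both visits, the plan would not say which key feeds Models 2 and 3.

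Third, some steps are inferences. Separate IRT calibration follows only from the statement that the procedure is similar. Percent reduction is not written in the response section, which works by citation and is exploratory. Standardising factor scores within each visit, which would force mean change to zero, is stated nowhere. The 24 and 20 item counts are invented for illustration.

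Fourth, a condensed article may leave detail to a fuller plan. That would cover silence. Here the text states a rule, two models retained for scoring, and then uses change between the visits.

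Finally, one might conclude that the arm-invariance test in the baseline model is pointless because randomisation equates the arms. That holds only within a trial. The test also covers drug classes pooled across trials, which randomisation does not equate, so it should stay.

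**Conclusion.** The concern holds in a limited form. As written, the factor section can give baseline and week-6 scores on different scales, with no planned test over time. The same may apply to IRT by inference. The network section is better protected, though only configurally and with a fallback.

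The exposed results are mean change, any trial-level SMD on the SD of change (about 6% either way in the illustration), and exploratory response if it is defined by change from baseline. There the rates shift markedly and the odds ratio less. These sizes rest on assumed item counts and a one-factor simulation. They show direction and order of magnitude, and do not predict what the pooled data will give. If the two models turn out to keep the same items and weights, the problem disappears.

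The primary pooled comparison, and the baseline-adjusted trial-level coefficient with a residual-SD d, are not biased by the mismatch and lose only slight precision. The factor section and the definition of Models 2 and 3 should be reconciled before analysis.

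**What to change.** - **One scoring key.** State one item set and one parameter set per method and instrument, estimated jointly over baseline and week 6. Apply it to all participants at both visits in Models 2 and 3, the trial-level analyses and the response analyses. Align the scoring sentences in the factor section with the baseline covariate named in Models 2 and 3.
- **Invariance over time.** Add a baseline-versus-week-6 test for the factor and IRT models, covering loadings and intercepts or thresholds. Keep the arm and sex tests.
- **If it fails.** Keep the common item set for the sum scores. For the weighted scores, use partial invariance with common anchor items as a sensitivity analysis.
- **Standardiser.** Divide trial-level effects by the residual or outcome SD, not the SD of change.

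The cost is some rewording and a joint two-visit model for each method. The common key may fit each visit slightly less well than that visit's own best model. The separate models can still be reported descriptively, as already planned.
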